
### Prior multisystemic therapy trials

The two promising MST-PSB trials [18, 32] were conducted in the United States by the developers of the intervention, and there are potential differences in recruitment, sample and the comparator condition when these trials are considered in relation to the UK context. The first efficacy trial [18] recruited participants exclusively from the juvenile justice system who had been adjudicated for a sexual offence, and the sample was also characterized by high rates of non-sexual offending. All participants in the comparison condition received non-manual-driven group cognitive-behavioural therapy (CBT). Although CBT does not have a well-developed evidence base for juvenile sexual offenders, it has proved efficacious when applied to several child mental health conditions such as anxiety [36, 37] and posttraumatic stress disorder [38]. CBT is also the preferred treatment approach for treating adult offenders (see [20]). By contrast, while the larger community-based MST-PSB effectiveness trial in the United States [32] also recruited participants solely from the juvenile courts system, the TAU was sex-offender-specific group treatment provided by probation, with a minority of participants accessing private mental health treatment.

In the United Kingdom, juvenile sex offenders are identified and receive mental health support and treatment through youth offending services and social care, where they are identified as being high risk, and in need of intervention and potentially out-of-home placement for safety reasons. Given the different ways in which young people displaying sexually harmful behaviour are referred in the United Kingdom, it is possible that participants in the UK trial will differ from their counterparts in the United States in the nature and severity of their problem sexual behaviour, as well as their co-occurring mental health disorders and problems. For example, mental health systems for identifying and treating young people showing problematic sexual behaviours are underdeveloped [39], and therefore, it is possible that young people showing both problematic sexual behaviours and conduct problems may not be identified to the same degree as those in the United States. The interventions provided to these young people are also specific to the UK mental health, juvenile justice and social care systems (see ‘Management as usual’, below). Finally, and more broadly speaking, the two previous MST-PSB trials have collected secondary outcomes at one time point, immediately following treatment [18] or up to 1 year following the interventions [32]. In order to understand better the longer term individual, family and school adjustment of participants following intervention, data in these domains need to be collected at more frequent intervals and over a longer time period to determine the utility of MST-PSB in the United Kingdom.

### The current trial

This paper describes the protocol for the Services for Teens Engaging in Problem Sexual Behaviour (STEPS-B) trial, a UK feasibility evaluation of MST-PSB. The MST-PSB intervention uses the term ‘problem sexual behaviour’ to describe young people who display serious non-normative sexual behaviours that victimize others, which can be aggressive or non-aggressive sexual acts [40]. Gerardin and Thibaut [41] defined this behaviour as committing any sexual act with a person of any age against the victim’s will, or in an aggressive, exploitative or threatening manner, including non-contact sexual acts such as exposing one’s genitals or masturbating in public.

The STEPS-B trial aims to assess the feasibility of implementing MST-PSB and also the barriers to implementing it: young people who display problem sexual behaviour suffer intense stigma and blame [42]. There are also well-documented challenges to effectively identifying, assessing and intervening with this clinical population in the United Kingdom [43]. As well as evaluating the effectiveness of MST-PSB in a UK context, the aim of the trial is to determine whether MST-PSB can be implemented fully and at a scale that would warrant a full trial. This feasibility trial will follow rigorous RCT guidelines, and therefore, part of the evaluation will be to determine whether a stringent RCT is realisable, as there have been no previous RCTs of interventions addressing adolescent problem sexual behaviour in the United Kingdom.

The MST-PSB feasibility trial is being conducted at the Brandon Centre, London, a charitable organization serving the mental health needs of young people. The Brandon Centre is participating in the RCT as part of its funding agreement with the UK Department of Health for having a clinical team. In the run-up to the trial, clinicians at the Brandon Centre will have been working with MST-PSB families for at least 18 months. This represents a bedding-in period to help raise awareness of the Centre’s specialized service among referrers (youth offending, social care and child and adolescent mental health services [CAMHS]), as well as ensuring that the therapists are applying the therapeutic model of MST-PSB (see below) in accordance with MST principles and guidelines. The Brandon Centre developed expertise in delivering MST for general antisocial behaviour (‘standard’ MST) in the first RCT of MST in the United Kingdom [25] and has continued to provide standard MST in several localities in London since then. While the MST-PSB clinical service is provided solely by one team of trained therapists at the Brandon Centre, recruitment for the MST-PSB trial is occurring across five localities in London.

There are specific feasibility issues in implementing an RCT for problem sexual behaviour in the United Kingdom. These include the challenge of recruiting an adequate sample of adolescents displaying sexually problematic behaviour; the acceptability of an RCT to the key agencies and systems that are involved in managing these young people and in providing them with mental health services; the ability to identify comparable interventions specifically designed to target problem sexual behaviour (that is, MAU); and the acceptability of the research protocol to young people and their families, given the stigma associated with individuals who display problem sexual behaviour and high levels of anxiety within families and professional systems regarding the management and treatment of this behaviour.

While the social and fiscal costs of adolescent sexual offending are substantive and warrant the development of effective and evidence-based services, European epidemiological studies of adolescent sexual offending in Oxfordshire, UK [44] and Sweden [45] suggest that there are low base rates of sexual offending and referrals to social services, respectively. The results of the Oxfordshire survey of sexual offending by males 12 to 17 years of age, using a postal questionnaire, revealed a 1-year incidence of 1.5 official juvenile sexual offenders per 1000 males (0.85 per 1000 12- to 17-year-olds of both sexes) [44], whereas the Swedish national survey of all adolescent sex offenders 12 to 17 years of age referred to social services in the year 2000 yielded a 1-year incidence of 0.060 % (95 % confidence interval = 0.052-0.068), or six referrals per 10,000 adolescents [45]. At the same time, sexual offending rates based on adolescent self-report are likely to underestimate the incidence of sexual offending in this population given that this behaviour is illegal and associated with shame and stigma. This assertion is supported by estimates of adolescent sexual offending based on reports of victims of sexual abuse. In addition, referrals to social services by professionals may be influenced by their perceptions of whether effective services will be available once a referral is processed.

The available data on prevalence and the difficulty gaining accurate estimates of incidence and service use suggest that the size of the pool of available participants to recruit into an RCT for problem sexual behaviour is uncertain. Therefore, the success of the trial is likely to depend on efficient identification of potential participants. It will also rely on established systems for providing specialist treatments for adolescent sexual offenders and for managing their mental health needs, given that judicial processes can determine the offenders’ availability for mental health interventions or delay timely provision of treatment. Two recent reviews of the provisions for juvenile sexual offenders in the United Kingdom noted that, despite examples of good practice, services for identifying and intervening with young people displaying problem sexual behaviour are underdeveloped [39]. For example, a recent examination of multi-agency responses to children and young people who sexually offend concluded that identification of young people’s problem sexual behaviour was often subject to disbelief, minimization and denial by professionals and by families; that much work was characterized by poor communication between the relevant agencies, with inadequate assessment and joint planning; and that cases were slow to get to court, on average taking 8 months between disclosure and sentencing, resulting in lengthy periods when little or no work was done with the young person [43]. The findings from this joint government inspection suggest that implementation of the MST-PSB trial will require substantial liaison and problem-solving with all relevant stakeholders to help identify young people who are appropriate for the trial and would benefit from the available interventions, as well as planning to accommodate judicial processes that will impact on the timely provision of both MST-PSB and MAU interventions.

Finally, the feasibility of the MST-PSB trial will undoubtedly depend on the acceptability of the research protocol to young people and their families. The research protocol for the MST-PSB trial, including the majority of the measures that will be administered to young people and their carers, has been successfully implemented with a diverse and large sample of young people showing antisocial behaviour and their carers in the START trial of standard MST [28]. However, the process of obtaining informed consent in the MST-PSB trial will depend on (1) a discussion between the young person and their carer(s) with an MST supervisor and a senior research assessor (RA), (2) details of the young person’s problem sexual behaviour, and (3) the completion of questionnaires by the young person and their carer(s) that involve details of their sexual development, including potential atypical sexual interests. It is possible that the young person and their carer(s) may be hesitant to participate in this process, given that the subject matter is highly sensitive, stigmatizing and often unknown to the wider community, and that adolescent problem sexual behaviour engenders high levels of anxiety in families and professional systems [39]. It is likely that effective relationships with the MST-PSB team, referral agencies, young people and their families will be paramount for the trial to be successful.

There are also several unresolved issues related to transporting MST-PSB to health and social care systems and jurisdictions outside the United States. In relation to a UK feasibility trial, the following issues require systematic monitoring: the clinical competence of therapists to practise MST-PSB in light of the curriculum differences for psychologists and social workers in the United Kingdom and the United States; the absence of data concerning the evidence base of usual services (that is, MAU) in the United Kingdom, given there are no prior RCTs of interventions for problem sexual behaviour in this country; differences in the motivation of MST therapists and the research team who were not involved the development of MST-PSB; and contextual issues such as differences in national standards with regard to sentencing policy and practice. In addition, while the sample sizes of studies with sexual offenders in general, and RCTs in particular, are relatively small, the larger MST-PSB effectiveness trial [32] provided no information regarding sample heterogeneity on key variables such as the presence or absence of non-sexual conduct problems [6] or the age differential between perpetrator and victim at randomization [10], both of which may influence the response to treatment.

### Aims

The aim of STEPS-B is to carry out a feasibility trial that will inform policymakers, commissioners of services and professionals about the potential for implementing MST-PSB as a programme for intervening with young people showing problem sexual behaviour. Should MST-PSB show potential in the United Kingdom context, the trial will determine what would be necessary to implement the programme more fully and at a scale that would warrant a full trial.

The trial will investigate whether MST is associated with the elimination or reduction of levels of sexual and nonsexual offending; reduction or elimination of problem sexual behaviours; reduction in nonsexual antisocial behaviour; less time spent in custodial institutions; and improved educational outcomes. It will also aim to establish the cost of MST-PSB relative to MAU, and the cost-effectiveness of providing this intensive form of intervention against the background of costs incurred in the 20-month period following randomization.

Finally, the trial will investigate specific feasibility issues that pertain to effective implementation of MST-PSB in the United Kingdom. These include: specific characteristics of young people’s problem sexual behaviour, where they are referred from, and what services have been or are being provided to them whether or not they are randomized into the trial; the beliefs and attitudes held by professionals around family intervention for this population, given that the young person will remain in the family home despite having committed sexually harmful behaviour towards other young people, including, in some cases, a sibling living in the same home; the degree to which professionals are supportive of the procedures and demands associated with an RCT research evaluation, including the randomization and its consequences; and the degree to which the institutions and agencies that manage young people showing problem sexual behaviour, such as the courts and child protection services, are able to support an RCT evaluation. It will also investigate the acceptability of the trial protocol to young people and their carers, and will gather information on their experience of MST-PSB and MAU interventions, through qualitative interviews following completion of treatment.

## Methods/Design

### Trial design

The STEPS-B trial is a single-site feasibility trial comparing MST-PSB with carefully documented MAU for adolescents who meet criteria for being at ‘high risk’ of requiring out-of-home placement, specifically when this risk is associated with problem sexual behaviour.

### Ethics

The study protocol was approved by the London-South East Research Ethics Committee (reference number 11/LO/0772). Research and development approval has also been sought and given for the Brandon Centre by Camden and Islington Research Ethics Committee (11/LO/1707).

### Study setting

The study will be conducted by the research team based at University College London (UCL). The team will be responsible for collecting data from cases referred to the Brandon Centre, London. Eighty families will be recruited to the study through referrals made to the Brandon Centre from at least five London boroughs. Referrals are anticipated from social care, CAMHS and youth offending services.

Participants will be recruited over 3 years. Recruitment will commence about 18 months after the therapists at the Brandon Centre have started working on MST-PSB cases; this initial period will allow MST-PSB therapists sufficient time to reach fidelity to the MST-PSB model before randomization begins. The team of three MST-PSB therapists is guided by a supervisor - a doctoral-level (or master’s-level with significant clinical and supervisory experience) therapist with sound knowledge of the theories and therapeutic practices underpinning MST-PSB and experience in providing MST clinical supervision. The MST-PSB supervisor conducts weekly group supervision, and one-to-one supervision of the MST-PSB therapists as needed, to ensure therapists are adhering to MST-PSB principles in their delivery of the intervention.

### Participants

Eighty participants will be recruited and randomly allocated, with half of the consecutive qualifying cases being assigned to MST-PSB and the other half to MAU.

### Sample size and power calculation

It is estimated that the Brandon Centre will have approximately two eligible cases per month, where referrals are obtained from a minimum of four boroughs, which would result in 72 cases randomized into the trial over the 3-year recruitment period. Five more boroughs are set to join the trial, resulting in nine boroughs in total; it is predicted that this will result in 34 eligible referrals per year, to give a total of approximately 102 cases randomized over 3 years.

Effect size has been estimated on the basis of the available data from a recent MST intervention study of sexual offenders in the United States [46]. As only summary statistics were available, 95 % confidence intervals for effect size were used and the lower limit chosen in a conservative approach. On the basis of the number of participants in the two groups who moved from offender to non-offender status during the follow-up period, the highly significant effect of treatment (*P* < 0.001, Fisher’s exact test) is 0.32 to 0.49 (Cramer, a medium to large effect). In the current study, non-offender status is defined as no arrest leading to conviction over the follow-up period, based on police computer records. We expect to achieve the lower end of the effect size range, given that the trial is mounted independently (although under the supervision) of the development team and involves the transportation of the clinical methodology across national boundaries, healthcare systems and cultures. A sample size estimate to give 80 % power based on the lower estimated effect size of 0.32 suggests 56 participants in a two-group design. Figure 1 shows the expected flow of participants from recruitment through to the end of the study.

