## Background

Systematic reviews of the prevalence of sexual abuse in young people indicate that 18 to 20 % of females and 6 to 8 % of males in the general population report having been abused before the age of 18 [1, 2]. Adolescents are the perpetrators of approximately 20 % of all sexual offences, and victim reports suggest that the proportion of juvenile offenders (versus adult offenders) increases as the age of the victim decreases [3]. Victims of sexual assault are at a high risk for negative sequelae [4, 5], and sexual offenders themselves engender significant social and fiscal costs, including removal from their family homes and impaired social, academic and vocational competencies as a result of their sexual offending.

Sexual offenders are heterogeneous [6, 7] and include a substantive subgroup who show many of the same risk factors as juveniles who engage in serious antisocial behaviour that does not include sexual offending [8]. For example, several studies have shown that sexual offenders share many of the same family and peer risk factors seen in non-sexual offending youth such as poor parent supervision, lower parental involvement and poorer parent-adolescent relationships, lower bonding to family and school, and higher involvement with delinquent peers [8, 9]. At the same time, a recent meta-analysis concluded that adolescent sexual offenders, when compared with adolescent non-sexual offenders, show greater atypical sexual interests (for example, sexual arousal to children or to coercive sex) and histories of child sexual abuse, higher levels of anxiety and lower self-esteem, and greater social isolation [10]. Correspondingly, while the sexual reconviction rates for adolescent sex offenders range from 5 to 14 % and are substantially lower than their reconviction rates for non-sexual offences (16 to 54 %) [11–13], reoffending rates for sexual offending are often associated with sex-specific factors [13–16], while non-sexual recidivism is related to factors commonly predictive of general delinquency [13, 15].

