### Multisystemic therapy as an intervention for problem sexual behaviours

MST is an intervention that has been developed in the United States. It has an established track record for successfully treating young people who show serious and persistent antisocial behaviour [22]. More recently, MST has been transported to other countries with some promising (Norway [23–25]) and mixed (Sweden [26] and Canada [27]) results. In the United Kingdom, following an earlier single-site trial of MST [25], a large multi-site trial is now underway, which is comparing MST with the usual services delivered to this population of young people (the START trial) [28].

Multisystemic Therapy for Youth with Problem Sexual Behaviours (MST-PSB) is an adaptation of MST aimed at adolescents who have committed sexual offences and demonstrated other problem behaviours. It is an intensive family- and home-based intervention uniquely developed to address the multiple determinants of problematic sexual behaviour in adolescents. MST-PSB is designed to reduce problematic sexual behaviours, antisocial behaviours and out-of-home placements. Problematic sexual behaviour in adolescents is sexual behaviour that is developmentally inappropriate or potentially harmful to the self or others and includes behaviour of a sexual nature that infringes on the rights of others (such as the use of coercion or force) [29].

Recent reviews of the sexual offending outcome literature [17, 30, 31] have noted that two RCTs of MST-PSB are the only published and peer-reviewed RCTs to evaluate the effects of the intervention on juvenile sexual offending, and that they have produced promising findings [18, 32]. A small efficacy trial conducted by the developers of MST-PSB reported that juvenile sex offenders receiving MST were significantly less likely than those receiving usual services to be rearrested for either sexual offences (8 % versus 46 %) or nonsexual offences (29 % versus 58 %) at 8.9 years post-treatment, and to have spent 80 % fewer days in confinement facilities [18]. A larger effectiveness trial studying the impact of MST-PSB compared with usual services through a 12-month follow-up period reported that adolescents receiving MST-PSB engaged in less problem sexual behaviour and were less likely to be placed out of the home [32].

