MST-PSB is therefore the only evidence-based intervention currently available for adolescents showing problem sexual behaviour. However, despite some initial positive findings, there are several unresolved issues relating to transporting MST-PSB to other health and social care systems and jurisdictions outside the United States. First, the effectiveness of MST-PSB needs to be carefully assessed in the UK mental health, juvenile justice and social care systems. The pattern of results found in the transportability of RCT evaluations of standard MST in Canada and Europe suggest that the effectiveness of MST-PSB needs to be demonstrated by independent investigators and outside the United States. Specifically, the magnitude of the associations between standard MST and treatment outcomes are substantially higher in trials that involved the developers of the intervention (effect size = 0.81) than in studies conducted without their close involvement (effect size = 0.27) [33], suggesting a possible ‘developer effect’ (for example, therapists supervised by developers adhere more to the MST guidelines or are more motivated and engaged). Thus, an independent transportability trial is necessary to demonstrate that MST-PSB can be delivered with fidelity by UK-trained therapists. This is crucial, given that the MST-PSB adaptation requires additional skills and practices that are not part of standard MST, such as addressing parents’ and adolescents’ denial of problematic sexual behaviour. Furthermore, the intervention is being applied by MST therapists to a highly stigmatized population against which there are very strong cultural biases and prejudices. The clinical competency of UK psychologists and social workers to deliver MST-PSB with fidelity, relative to their counterparts in the United States, may also be influenced by curriculum and training differences. In addition, the relative success of standard MST may be due to the relative quality of the usual services for managing antisocial behaviour in the United States compared with usual services in other countries. MST may produce better outcomes only when usual services produce weak, null or even negative effects. Thus, the superiority and cost-effectiveness of MST-PSB needs to be demonstrated outside the United States, in studies where the therapists delivering MST are independent of the MST-PSB developers, where the comparison services or ‘management as usual’ (MAU) is consistent with the options currently available for young people showing problem sexual behaviour in that region, and where the sentencing policy within the justice system does not result in comparison with alternatives such as custodial sentences. Moreover, as noted by Littell [34] following a detailed Cochrane review of the effectiveness of MST [35], it is crucial that the research evaluation team and the developers who deliver the clinical service be completely independent.

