### Primary outcome

The primary outcome of the proportion of cases where a sexual offence has been incurred during the follow-up period will be described by a Kaplan-Meier graph and summarized by the proportions in each group with a new sexual offence by 20 months. The linked outcome of out-of-home placement will also be described by a Kaplan-Meier graph and summarized by the proportions in each group with out-of-home placement by 20 months. The number of events will be estimated in order to inform power calculations for a fully powered efficacy trial.

For time-to-event offending outcomes, the event rate will be estimated. For continuous secondary outcomes, such as questionnaire data, linear mixed effects models will be fitted in order to estimate the individual-level residual variance.

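### The 80% power at an effect of 0.32 was set for general offending and does not carry over to the sexual-offence outcome that the analysis section calls primary

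*Protocol article*

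**What the plan says.** In the protocol article, Sample size and power calculation, the effect is taken from a US MST study of sexual offenders. It is based on the numbers who moved from offender to non-offender status, and the treatment effect "is 0.32 to 0.49 (Cramer, a medium to large effect". The same section defines a non-offender in STEPS-B as someone with no arrest that ends in conviction on police computer records. It does not restrict this to sexual offences. The lower limit is adopted ("We expect to achieve the lower end of the effect size range"). The result is "A sample size estimate to give 80 % power", where the "lower estimated effect size of 0.32 suggests 56 participants in a two-group design". No alpha, sidedness or test is given.

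The Primary outcome part of the Statistical analysis plan starts from a different endpoint: "The primary outcome of the proportion of cases where a sexual offence has been incurred during the follow-up period". It is summarised by Kaplan-Meier curves and by the proportion in each arm at 20 months.

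On the likely frequency of that endpoint, the Background says that "the sexual reconviction rates for adolescent sex offenders range from 5 to 14" %, against 16 to 54% for non-sexual reconviction. It gives no follow-up length.

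Two other places name the primary outcome differently. Under Assessments and outcome measures, Primary outcomes, it is documented offending of any type. In the abstract it is out-of-home placement.

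**The concern.** An effect expressed as Cramer's V cannot be moved from a common outcome to a rare one without checking that it can be reached. In a two-by-two table with equal arms, V is capped by the control rate: if few control participants have the event, even complete prevention gives a small V. The effect here was set for conviction of any kind, while the analysis section names an outcome that the document itself describes as much rarer.

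At stake is how the sexual-offence result will be read. Someone who takes the sample size section and the analysis section together would conclude that 80 participants are more than enough for the stated primary outcome. The Discussion strengthens that impression by describing the study as a robust test of effectiveness.

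**Working it through.** **Inputs.** V = 0.32, 80% power and 56 participants (Sample size and power calculation); 80 participants (Participants); 1:1 allocation (Randomization and procedures to minimize bias); sexual reconviction 5 to 14% and non-sexual reconviction 16 to 54% (Background). Assumption: two-sided 5% test, since none is stated.

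**1. The plan's own figure.** For a two-by-two table, N = (z_alpha + z_power)² / V².
- Two-sided 5%: (1.960 + 0.842)² / 0.32² = 7.85 / 0.1024 ≈ 76.6, so 77.
- One-sided 5%: 61.
- Treating 0.32 as a correlation (noncentral t): 71 two-sided, and 56 one-sided at 5% (power 0.803).

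So 56 is reproduced only under an unstated one-sided correlation test. The planned 80 exceeds 77, so for an outcome where V = 0.32 is realistic, 80 participants give about 82% power by the normal approximation.

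**2. Ceiling on V.** With equal arms, V = (p1 − p2) / (2·√(p̄(1 − p̄))), where p̄ = (p1 + p2)/2. With p2 = 0 this becomes √(p1 / (2 − p1)).

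| MAU rate | MST-PSB rate | V |
|---|---|---|
| 5% | 0% | √(0.05/1.95) = 0.160 |
| 10% | 0% | √(0.10/1.90) = 0.229 |
| 14% | 0% | √(0.14/1.86) = 0.274 |

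Setting V = 0.32 and solving gives p1 = 2(0.32²) / (1 + 0.32²) = 0.2048 / 1.1024 = 0.186. A V of 0.32 therefore needs a MAU rate of at least 18.6% together with no events on MST-PSB. At a MAU rate of 20% it still allows only 0.6% on MST-PSB.

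**3. Power for sexual offences (Fisher's exact test, two-sided 5%).** With no events on MST-PSB, significance needs at least 6 events in MAU, both at 28 per arm (6 v 0, p = 0.023) and at 40 per arm (6 v 0, p = 0.026).
- 14% v 0%, 28 per arm: P(Bin(28, 0.14) ≥ 6) = 0.19.
- 14% v 0%, 40 per arm: P(Bin(40, 0.14) ≥ 6) = 0.50.
- 14% v 7%, 40 per arm, summed over all tables: 0.09.

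The normal approximation is kinder at 14% v 0% (about 54% with 56 participants and 70% with 80) but still falls short of 80%.

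**4. Where 0.32 can be reached.** At 54% v 23%: 0.31 / (2·√(0.385 × 0.615)) = 0.32. At the bottom of the non-sexual range, 16% v 0%, V is only √(0.16/1.84) = 0.29. So 0.32 suits general offending at fairly high rates.

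**5. Precision with 40 per arm.** The 95% half-width for the risk difference at 14% v 7% is 1.96·√(0.14·0.86/40 + 0.07·0.93/40) = 1.96 × 0.068 = 0.133, or about ±13 points.

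**The case against.** The best defence is that 0.32 was never meant for sexual offences. The sample size section defines status by any conviction, and the Primary outcomes section, which names documented offending, also counts long-term placement against non-offender status. For that outcome 0.32 can be reached. This stands, and it locates the fault in the change of outcome between sections rather than in the calculation itself.

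A reader might go further and infer that 0.32 is impossible for sexual offences. The documents do not support that. The ceiling holds only while the true MAU rate is below 18.6%. The 5 to 14% range is for reconviction, with no follow-up length. The analysis section counts an offence rather than a conviction, the outcomes section adds reports from families and social care to police records, and entry requires risk of reoffending. The article also cites sexual rearrest of 8% versus 46%, a V of 0.43, though "at 8.9 years post-treatment" and in a small trial run by the developers, so it says little directly about 20 months. The ceiling also applies to the true effect: with 14% v 0%, a sample V of 0.32 or more still arises by chance with probability about 0.19.

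A reader might also shrink the effect to a third, because the article contrasts MST trials with and without developer involvement (0.81 v 0.27). Those figures concern standard MST on an unstated scale, so applying their ratio to a Cramer's V is not justified. Calling the choice conservative is literally accurate where it describes taking the lower confidence limit.

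Finally, no between-arm test of offending is planned. The analysis is descriptive, and event counts are meant to inform a later, fully powered trial. That limits the harm to a misleading power statement.

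**Conclusion.** The point holds in a conditional form and should be fixed. If the MAU rate lies in the document's own 5 to 14% range, the largest possible V for sexual offending is 0.16 to 0.27, below the planning value. Power is then at most about 50% with 80 participants even under complete prevention at the top of the range, and about 9% if the rate is halved from 14% to 7%. These power figures assume a two-sided 5% Fisher test and 1:1 allocation. The conclusion would change only if the MAU rate reached at least 18.6%, with no or almost no events on MST-PSB near that threshold; the article gives no basis for planning on this over 20 months. The 80% figure can be defended only for general offending at high rates, such as 54% v 23%.

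**What to change.** - Reconcile the primary outcome across the abstract, the Primary outcomes section and the Primary outcome part of the Statistical analysis plan.
- State in Sample size and power calculation that 0.32 and 80% power refer to any offending and do not apply to sexual offences.
- If sexual offence stays primary, replace the power claim with the precision that 40 per arm gives (95% interval for the risk difference about ±13 points at 14% v 7%), and report event rates by arm with 95% confidence intervals.

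The cost is text only: design, recruitment and data collection do not change. The stated power becomes less favourable.
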